### Hypothesis

The whole hypothesis was made based on the evolving model of Andersen's service utilisation behaviour model and Donabedian's structure-process-outcome paradigm to assess the health quality [27, 28]. We modified the health system structure referring to some suggested modification to adapt to the chronic cases [29–31]. We made two basic assumptions under the transduction pathways from hypothesis to conclusion: (1) the integrated health service delivery would improve health outcomes through providing more coordinated care, and the system efficiency would then improve from better primary and community care; (2) the payment system would help to change the supplier behaviours and exemplify the outcomes. Assumption 1 would be proved from comparing treatment groups with the control group; and Assumption 2 would be proved from comparison within this two treatment groups (see Figure 2).

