#### System global budgets and pay-for-performance (SGB and P4P)

Though MIP and MDT were designed to form a new patient-centred service model, the behind motivation to make it run effectively was still needed. Originally, the suppliers were paid separately from the medical insurance fund without considering if they cooperate, in this case, they would be granted reimbursement whether they performed duplicated exams, prescribed contradictory medicine or had bad control of discharged patients. The whole concept of SGB–P4P system was to better integrate the primary care fund and medical insurance fund together, and to stimulate team staff from different institutions to act for the patient interest. The basic process was: first re-calculating the possible medical consumption per capita in a certain period, and pre-paying the MDT team as a whole without identifying where they came from; second paying based on the cooperation performance; third promising the re-distribution autonomy of the possible savings and paying according to the previous distribution plan. The medical fund officer kept the right to evaluate the team performance, monitor the money re-distribution plan and randomly check to make sure the patients were treated properly. The logic behind the payment system was to encourage the dominant attention on clinical service gradually transfer into the primary care, and avoid inappropriate and unnecessary treatment to the greatest extent by integrating the suppliers into a shared group and force them to think and act for the patient good as much as possible.

To sum up, the MIP was designed to afford a behaviour benchmark, the MDT was designed to distribute role responsibility, and the SGB–P4P was designed to make it effectively and consistently run.

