### Sampling and randomisation

Six towns were selected randomly from the 24 rural communities and then were categorised into three groups with a combined consideration of population size, social development and distance. Because there were obvious potential confounders in social experiment, the towns were first categorised into two types based on comprehensive consideration of socio-economic development level and hospital ability, two basic confounders which we assumed high relevance with the intervention outcome. The socio-economic development level mainly indicated the patient population, their per capita income and average distance from the location to downtown (translated into traffic time by public transportation). The hospital ability represented resource possession and staff skills. Second, every two towns of each type were randomly assigned into treatment/control groups to ensure group comparability. These two steps were done to make sure towns comparable both within groups and within cluster types in case of different comparison need.

In patient sampling, we used three-stage stratified random sampling strategy instead of propensity scoring matching, concerning the complexity of sampling and excessive workload. We chose gender, age and risk level as the three stratify factors. Risk level was a comprehensive factor that summing up the BP/GLU level as well as the possible risky factors due to the patient lifestyle. The hypertension and diabetes II patients were divided into three and two risking groups before the baseline, and we stratified the patient library mainly in accordance with the original files but with a slight alternation based on professional re-assessment after personal contact at the baseline.

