#### Structure measures: “system efficiency”

The system efficiency mostly refers to the compare relation of medical expenditure of county–to–township hospitals, including inpatient visits, in-patient fee, average length of stay, average cost per case, average exams per case and the average use of necessary medicine. And integration degree of MDT is measured by the Integration Degree Questionnaire evolved from D'Amour's collaboration typology model [33].

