### Analysis strategy

#### Statistical analysis

There are two-stage analyses in this trial. First, we will use difference-in-differences (DID) model [34] to examine the effects of the intervention; second we will use structural equation modelling (SEM) [35] to explore the hidden effecting pathway of how the intervention works.

The DID model is often used to exclude out the time effect and group differences. In the pilot study, we had mimicked the regression tendency of BP falling to ensure a similar time effect in groups. In the main study, we mainly include three explanatory variables in the regression model: group, time and interaction term between group and time. And to exclude the intra-cluster correlation (ICC) from non-independent clustering and cross-level interaction, we choose three-level regression model to control for the potential confounders of the context effect. For other repeatedly measured outcomes like BP control, lifestyle changes and professional behaviours we mainly use three-level and repeated measure multivariate analysis of variance to examine the group differences. The three levels we consider are: level 1 – individual, level 2 – cluster/village, level 3 – group. Data analysis will be carried out on the Stata (IC: 13.1). In SEM we hope to establish an explainable relationship between intervention effect of health outcome and design effect of payment system reform.

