#### Process evaluation

We first use contextual analysis to describe the fundamental environment of the delivery system in the trial place, and then demonstrate the intervention process on organising MDTs, MIPs and implementing SGB–P4P. We will especially focus on the possible obstacles which would potentially hinder the implementation of intervention strategy. Then we will mainly discuss the effecting pathway of payment system to health outcomes, and emphasise on key elements of behaviour model from both suppliers and utilisers side. At last by following cause–effect paradigm, we use evidence to prove our assumption and hypothesis. Relative resources and materials are collected from document files, behaviour observations and stakeholder interviews; data analysis will be processed using structured narrative analysis.

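### Payment varies only between towns (two against two) and the stated model levels omit town, so the structural equation model cannot validly test the payment pathway

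*Protocol article*

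**What the plan says.** The Hypothesis section states the mechanism: "the payment system would help to change the supplier behaviours and exemplify the outcomes". It also names the comparison that is to settle it: "Assumption 2 would be proved from comparison within this two treatment groups".

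Under Sampling and randomisation, "Six towns were selected randomly from the 24 rural communities and then were categorised into three groups", and towns of each type were then randomly assigned to the groups. The section on system global budgets and pay-for-performance describes the payment as "pre-paying the MDT team as a whole without identifying where they came from". Payment is therefore constant within a town.

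The Statistical analysis section introduces the SEM as follows: "second we will use structural equation modelling (SEM) [35] to explore the hidden effecting pathway of how the intervention works". It closes with the aim: "In SEM we hope to establish an explainable relationship between intervention effect of health outcome and design effect of payment system reform". The same section lists the levels of the regression model as individual, cluster/village and group. It states no data level, mediator, estimator or clustering term for the SEM.

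Supplier behaviour is measured in several ways. Under Process measures these include referrals, communication intensity, unnecessary exams per capita, referral and waiting times, staff satisfaction and a continuity of care index (COCI) built on a patient's own contacts. Under Structure measures, "integration degree of MDT is measured by the Integration Degree Questionnaire".

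**The concern.** The pathway of interest runs from payment to supplier behaviour to patient outcome. The first step compares units that differ in payment, and those units are towns. Sampling more patients or villages inside a town adds no information on whether payment changed behaviour, because every patient there lives under the same payment system. Any other lasting difference between the towns enters the comparison in full.

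A model that counts patients, or villages, as independent gives this step a standard error that is far too small. The only level structure in the article stops at village and then jumps to group, so carrying it over to the SEM would leave that problem in place. At stake is the second of the two named analyses, also announced in the abstract, which is aimed at a policy claim about how payment reform works. The primary outcomes are not affected by this point.

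**Working it through.** **The plan's own figure.** No power or sample size is given for the SEM. The one figure that can be checked is the note to Table 2: 120/96 or 120/120 cases give over 80% power for a difference of 0.20. With two-sided 0.05 and rates of 0.5/0.3, 0.6/0.4 and 0.7/0.5, power is 0.837–0.853 and 0.877–0.890. The statement is reproduced, but for independent individuals with no design effect.

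**Inputs.**
- Six towns in three groups: two per group, assuming equal groups.
- Patients: 1641 + 332 = 1973, so 1973/6 ≈ 329 per town. This assumes that the hypertension and diabetes counts do not overlap and that towns are of equal size.
- Intraclass correlations (ICC): none given. Assumed for the outcome at town level: 0.01–0.05. For the supplier measure, assumed from a town ICC of 0.05 up to one value per town.

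**Payment to behaviour, patient-level analysis ignoring clustering, no true effect.**
- Supplier measure varying between patients, town ICC ρ: design effect DE = 1 + 328ρ; false-positive rate = 2[1 − Φ(1.96/√DE)]. At ρ = 0.05, DE = 17.4 and the rate is 64%. At ρ = 0.20, DE = 66.6 and the rate is 81%. Simulation gives 61–65% and 81–83%.
- Supplier measure with one value per town, four towns: the naive t equals the town-level t (2 df) times √(1314/2) = 25.6, where 1314 = 4 × 329 − 2. It passes 1.96 when the town-level |t| exceeds 1.96/25.6 = 0.0765. For 2 df, P(|t| > c) = 1 − c/√(2 + c²) = 1 − 0.054 = 95%. Simulation gives 94–95%.

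**Villages modelled, town omitted** (simulation, 10 villages per town). The first step is falsely significant in 63–70% of trials with one value per town. It is 32–37% when 70% of the measure's variance lies between villages (assumed).

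**Whole indirect path** (both steps significant, no true effect, patient-level regressions):

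| Supplier measure | Towns | Outcome town ICC 0.01 | Outcome town ICC 0.05 |
|---|---|---|---|
| One value per town | 4 | 35% | 63% |
| One value per town | 6 | 33% | 59% |
| 70% of variance between villages | 4 | 15% | 30% |
| 70% of variance between villages | 6 | 18% | 38% |

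The rows above also include a village ICC of 0.02 for the outcome. For a measure varying between patients, the whole-path rate over the same outcome ICCs is about 4–8% at a town ICC of 0.05 for the measure, and about 8–24% at 0.20. Across all runs the range is about 4–64%.

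**What the towns can support.** Two against two gives 4 − 2 = 2 df and a critical t of 4.30. There are 6 ways to split four towns two and two, so the smallest two-sided permutation p is 2/6 = 0.33. If towns are assigned within type there are 4 ways, and it is 2/4 = 0.50. With all six towns in three groups there are 3 df and the critical t is 3.18.

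**The case against.** The strongest reply is that the article does not say how the SEM will be fitted. It condenses a fuller plan, and silence on the SEM's level is no error. The analysis is also introduced as exploration. This stands in part: a patient-level SEM is one possible reading, so the error rates are conditional. But the number of towns is fixed by the design, and no later specification adds units to the payment step. Where the article does name levels, town is absent.

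Three stronger readings are tempting, and the documents do not support them.
- A reader might infer that team cooperation takes one value per town, so that the entire path rests on four to six points. Nothing says so. COCI, referrals and unnecessary exams can vary between patients, and communication and satisfaction between staff. The behaviour-to-outcome step can therefore use variation inside towns.
- A reader might infer that the SEM will report a mechanism almost regardless of the truth. Only the first step has error rates near that. The whole-path rate is close to nominal when the supplier measure varies mostly between patients.
- A reader might attach "we use evidence to prove our assumption and hypothesis" to the SEM. That sentence belongs to the Process evaluation, which is a structured narrative analysis. Assumption 2 itself is to be settled by comparing the two treatment groups.

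**Conclusion.** The point holds in a limited form, as an inexpensive improvement. That payment varies only by town follows from the design and needs no assumed ICC; so does the limit of 2 df and a smallest permutation p of 0.33 or 0.50, given two towns per group. The error rates rest on assumed ICCs and on an analysis that leaves town out. For the payment-to-behaviour step, every scenario examined lies far above 5%. For the whole path, the result depends mainly on how much of the supplier measure's variance lies between towns. The SEM remains useful for relations inside towns, but it cannot establish that payment works through supplier behaviour.

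**What to change.** 1. Report payment to supplier behaviour as the six town values at baseline and end-line, labelled descriptive or hypothesis-generating, without a patient- or village-level p-value.
2. Limit SEM inference to within-town relations, using town indicators or town-centred variables with village-clustered errors. Relate patient outcomes to mediators that vary inside towns: COCI, referrals and unnecessary exams, as well as awareness, self-efficacy, lifestyle and follow-up. State that these relations do not test the payment effect, since centring by town removes all variation in payment.
3. In the Statistical analysis section, replace the verb establish by explore or describe for the payment pathway. The Process evaluation section needs no change on this ground.

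The cost is a few sentences and a simpler SEM; no new data are needed. The trial gives up a formal test of the payment pathway, which six towns cannot support.

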#### Process evaluation

We first use contextual analysis to describe the fundamental environment of the delivery system in the trial place, and then demonstrate the intervention process on organising MDTs, MIPs and implementing SGB–P4P. We will especially focus on the possible obstacles which would potentially hinder the implementation of intervention strategy. Then we will mainly discuss the effecting pathway of payment system to health outcomes, and emphasise on key elements of behaviour model from both suppliers and utilisers side. At last by following cause–effect paradigm, we use evidence to prove our assumption and hypothesis. Relative resources and materials are collected from document files, behaviour observations and stakeholder interviews; data analysis will be processed using structured narrative analysis.

## Discussion

This is the first trial in both developing countries and rural areas to gather evidence of health policy reform on delivery and payment system integration using experimental design. Previous studies on chronic disease management mostly focused on clinical and technical novelties, and did not develop inter-systems vision and strategy when reforming the delivery system [36, 37]. Although there were researches which had already proved the importance of simultaneous payment system intervention on changing delivery system [38–40], we still do not know in what way and to what extent can it affect the health outcomes. Thus, through this trail we first hope to build a feasible policy package to help health system integration, and then we want to identify the barriers and facilitators during implementation of professional/organisational collaboration on community chronic disease management. By doing this, we especially expect to prove the importance of integrated and systematic thinking when making decisions of health policies. The outputs will be an integrated care model of community-based chronic disease control, including policy packages of clinical guidelines, team guideline and financial stimulation plan. With the fundamental environment analysis we hope this model can be generalised to or at least give some hints to other LMICs/rural areas which are facing with similar problems.

The trial design has some potential limitations. Initially, we were going to use randomised controlled trial which may provide the highest level of evidence even in social science experiment as many previous studies in China succeeded to [41–43]. However, the intervention strategies we designed in this trial will not succeed without the acknowledgement in each cluster, which means the randomisation process might sacrifice a little. As a result, the proof power may be reduced. To compensate, we controlled the potential contextual and individual confounders during the grouping and sampling period to achieve a maximum control of cases. Second, though a latest systematic review pointed out that there was no evidence to prove that the multifaceted interventions were more effective in changing the health care professionals' behaviours [44], still several experiments had shown better effects of multifaceted interventions on hypertension and diabetes II patients [45–47].

## Conclusion

As it is a strong belief that “the real change in all kinds of reforms is the change of people”, it is extremely attached importance to the professional collaboration in the health integration reforms area. With various theory and practice of nowadays integration reforms, we choose the integration between primary care and clinical treatment in delivery system, and designed this trial based on community chronic patient, exploring the possibility of cooperation behaviour among multidisciplinary and multi-institutions. With further data analysis, we will provide evidence not only on evaluation of the impact of interventions to improve the integrated care, but also evaluation of the effects and efficiency of improved integration.

## Figures and Tables

**Figure 1. fg0001:**
[figure not shown]
Map of China, Chongqing and Qianjiang: geographic distribution of trial places.

**Figure 2. fg0002:**
[figure not shown]
The study hypothesis, assumptions and proof paradigm.

**Figure 3. fg0003:**
[figure not shown]
MDT: re-construction of the health human resource in three levels.

**Figure 4. fg0004:**
[figure not shown]
MIP: re-enactment of the organisation collaboration and patient flow.

**Table 1. tb0001:**
[figure not shown]
Group intervention strategies

**Table 2. tb0002:**
[figure not shown]
Minimum cases needed under index “continuity of clinical service”

Summary: group cases of 120/96 or 120/120 in treatment/control group could achieve over 80% power to detect a 0.2000 difference between group proportions.

^a^Considering the intervention effect, we assumed the relation of conforming cases between control/treatment group varied from 0.8–1.0/1.0.

^b^Assumed the detectable proportion of cases conformed to the defined “continuity of clinical service” is 0.5–0.7 in the treatment group and 0.3–0.5 in the control group.

**Table 3. tb0003:**
[figure not shown]
Possible statistical power of main variables

**Table 4. tb0004:**
[figure not shown]
Result of grouping and patient sampling

Note: ① Type A for better cluster: larger and richer; type B for worse cluster: smaller and poorer. ② H for hypertension; D2 for diabetes 2. ③ Population, patient population and sample size are not averaged under “total average”. ④ All variables are compared with treatment group 1. ⑤ Distance is transferred into traffic time by public transportation. Time varies in accordance to the cluster terrain instead of linear map distance.

**Table 5. tb0005:**
[figure not shown]
Outcomes, definition and data collection
